# Recognition of intracranial hypertension using handheld optical coherence tomography in children (RIO Study): a diagnostic accuracy study protocol

**DOI:** 10.1136/bmjopen-2021-048745

**Published:** 2022-01-11

**Keywords:** ophthalmology, paediatric neurosurgery, paediatric ophthalmology, paediatric plastic & reconstructive surgery, neuro-ophthalmology, paediatric neurology

## Abstract

**Introduction:**

Paediatric intracranial hypertension (IH) is a rare but serious condition that can pose deleterious effects on the brain and vision. Estimating intracranial pressure (ICP) in children is difficult. Gold standard direct ICP measurement is invasive and carries risk. It is impractical to routinely perform direct ICP measurements over time for all children at risk of IH. This study proposes to assess the diagnostic accuracy of handheld optical coherence tomography (OCT), a non-invasive ocular imaging method, to detect IH in children.

**Methods and analysis:**

This is a prospective study evaluating the diagnostic accuracy of handheld OCT for IH in at risk children. Inclusion criteria include clinical and/or genetic diagnosis of craniosynostosis, idiopathic intracranial hypertension, space occupying lesion or other conditions association with IH and age 0–18 years old. Exclusion criteria include patients older than 18 years of age and/or absence of condition placing the child at risk of IH. The primary outcome measures are handheld OCT and 48-hour ICP assessments, which will be used for diagnostic accuracy testing (sensitivity, specificity, positive predictive value, negative predictive value and accuracy). Main secondary outcome measures include visual acuity, fundoscopic examination, contrast sensitivity, visual field testing and visual evoked potentials, wherever possible.

**Ethics and dissemination:**

Ethical approval was granted for this study by the East Midlands Nottingham 2 Research Ethics committee (UOL0348/IRAS 105137). Our findings will be disseminated through presentation at relevant meetings, peer-reviewed publication and via the popular media.

**Trial registration number:**

ISRCTN52858719

Strengths and limitations of this studyThis the first diagnostic accuracy study protocol using handheld optical coherence tomography (OCT) to detect intracranial hypertension in at risk children.This protocol promotes transparency of our methodology and reduces the risk of duplication.Fully automated handheld OCT image analysis is not currently available and manual segmentation takes longer, although our evidence-based methodology features semiautomated segmentation.Although handheld OCT can provide in vivo imaging in infants without sedation, it could be especially challenging in this patient population, which could limit imaging success rates.Gold standard intracranial pressure measurements form our reference standard, but these are only performed in select patients, thus limiting our overall recruitment.

## Introduction

### Intracranial hypertension

First described by Quincke in 1896, intracranial hypertension (IH) remains an area of major importance among the medical profession.^1^ If undetected and untreated, IH can pose devastating consequences including visual impairment, cognitive impairment, disability and even death.^2 3^ This is of particular significance in subacute conditions affecting children, because insidious elevation of intracranial pressure (ICP) may only be detected after insult to the brain and vision has already begun.^2 4^ Therefore, it is crucial that IH is detected and treated as early as possible to prevent the sequelae of IH.

The incidence of IH is approximately 0.63–0.71 per 100 000 children.^5 6^ IH can be categorised as primary, also known as idiopathic intracranial hypertension (IIH), and secondary; the former is characterised by elevated ICP with no identifiable cause, while the latter is characterised by elevated ICP directly resulting from another condition.^4 7^ Common associations of primary IH include female sex, high body mass index (BMI) and postpubertal status; however, it can occur in children with no predilection for sex or high BMI.^4 8–14^ Examples of secondary IH include expansive skull pathology, that is, space occupying lesion or hydrocephalus, or constricting skull pathology, such as craniosynostosis, characterised by the premature fusion of cranial sutures.^2–4^

### Measuring ICP

Measuring ICP in children presents a number of challenges. The gold standard method is direct intraparenchymal measurement, but this involves hospital admission and carries significant risks including infection, bleeding, cerebrospinal fluid (CSF) leak, mechanical failure and general anaesthesia risks.^15^ Another limitation of intraparenchymal measurement is the difficulty in obtaining repeated measures over time. Furthermore, there is no clinical consensus on timing, frequency and duration for accurate measurement, or what figure constitutes raised ICP in children. Many consider ICP greater than 15 mm Hg to be elevated,^2 16–24^ but Hayward *et al*^25^ argue this could reasonably be raised to 20 mm Hg.^25^ Overnight ICP monitoring during natural sleep, which provides a ‘grand average’ with description of the dynamics of the ICP, is considered the gold standard.^26^ In Great Ormond Street Hospital for Children (GOSH), London, monitoring is performed using an ICP bolt (Raumedic AG, Helmbrechts, Germany) for 48 hours according to clinical discretion, particularly in children with clinical suspicion of IH where ophthalmological findings, including fundoscopic and electrodiagnostic findings, are equivocal. This represents an important patient cohort where a more sensitive non-invasive measure could improve clinical decision-making and reduce the need for invasive ICP bolt monitoring. However, the youngest in this group undergoing ICP bolt monitoring are typically toddlers and older, whereas those aged under 1 year with conditions such as craniosynostosis typically undergo surgical treatment expectantly rather than having ICP bolt monitoring.

The ideal measure of ICP would be non-invasive, acceptable for children, quantitative and would permit serial measurements to appreciate evolving changes related to rising ICP. Existing surrogate measures of ICP do not fulfil all these criteria, including fundoscopy,^27^ radiography^28^ and ocular ultrasonography,^29^ each failing to provide adequate sensitivity to be used as screening tools. In particular, funduscopy is routinely used in paediatric ophthalmology clinics to detect IH. Tuite *et al*^27^ demonstrated that fundoscopy yielded sensitivity of only 22% for IH in children with craniosynostosis aged under 8 years old, while specificity was 98%. Hence, papilloedema detected on fundoscopy reliably indicates IH in younger children with craniosynostosis, but crucially its absence does not exclude IH.

### Optical coherence tomography

The optic nerve is primarily intracranial; hence, IH can cause optic nerve swelling with secondary retinal changes. Optical coherence tomography (OCT) is a non-invasive imaging modality that can rapidly produce ultra-high-resolution cross-sectional images of the optic nerve and retina in vivo.^30^ OCT scans of the optic nerve head (ONH) can provide highly reproducible quantitative measures associated with IH within seconds.^31^ Adult studies have demonstrated the value of OCT in IH, including volumetric analysis.^32–34^

Our recent systematic review^35^ revealed 21 studies using OCT to assist diagnosis and management of IH in children with craniosynostosis, IIH, space occupying lesion and other pathology. This review revealed generally good diagnostic capability for OCT, but no level 1 evidence was identified. There was inconsistency in OCT parameters and reference standards used, with no study featuring overnight ICP bolt monitoring. Validating prospective research is therefore required to determine optimal OCT parameters in this role and to develop formal clinical guidelines. Moreover, no studies used handheld OCT in children with craniosynostosis, IIH or space occupying lesion.

### Handheld OCT

OCT has revolutionised the clinical practice of ophthalmology over the past two decades. However, infants and young children have previously been largely deprived of this technology as conventional OCT machines were designed for adults, requiring compliance with a chin rest, good fixation and cooperation. These limitations have been overcome with the recent advent of the handheld spectral-domain OCT designed for infants, which is demonstrably reliable in awake infants.^30 36^ Normal development of the optic nerve^37^ and retina^38^ in children has recently been described using handheld OCT. A wide range of conditions have also been investigated using handheld OCT in children, including retinopathy of prematurity,^39^ nystagmus,^40^ foveal hypoplasia,^41^ optic nerve hypoplasia,^41^ achromatopsia,^42^ albinism,^43^ primary congenital glaucoma,^44^ microcephaly,^45^ craniopagus twins^46^ and others.

More recently, we performed a feasibility and repeatability study^47^ using handheld OCT in children with craniosynostosis (n=50, median age 51 months, age range 2–157 months). We found good feasibility, with 86% achieving at least unilateral OCT and 76% achieving bilateral OCTs of the ONH. This was higher than the success rate in healthy children found by Patel *et al*^37^ (70% achieving at least unilateral OCT imaging of the ONH). Factors boosting the likelihood of success in children with craniosynostosis included good understanding and cooperation of the child and parent/guardian and availability of an assistant. We also performed repeatability analysis in 20 children and found good repeatability (intraclass correlation coefficient range, 0.77–0.99; the majority exceeded 0.90).

Advantages of using handheld OCT in children at risk of IH include the following:

Handheld OCT can be performed in awake babies and infants, without the need for general anaesthesia.Even if under general anaesthesia, handheld OCT can be performed in a child lying down, both in the supine and lateral decubitus positions.Handheld OCT scans can be easily repeated in the clinical setting, enabling the assessment of evolving changes over time.Handheld OCT semiautomated segmentation parameters can be fully controlled by the investigator.^37 38 47^

## Objectives

### Primary objective

To assess the diagnostic accuracy of OCT for paediatric IH.

### Secondary objectives

To assess success rates of handheld OCT in children with craniosynostosis and other children at risk of IH.To evaluate ophthalmological outcomes, including visual acuity (VA), in this cohort and to compare these with corresponding OCT data.To characterise ONH and retinal morphology in conditions associated with paediatric IH.To compare repeated OCT data between clinic visits±ICP assessments±cranial vault expansion surgery±follow up, with ICP assessments wherever possible.To compare OCT data in children at risk of IH with that of healthy age-matched controls from our ongoing paediatric handheld OCT normative database.^37 38^

## Methods

### Study design

Single-centre, prospective diagnostic accuracy study.

### Subjects

Children aged 0–18 who are diagnosed with conditions associated with IH, including craniosynostosis of all forms (syndromic and non-syndromic), IIH, space occupying lesion and others.

### Recruitment

Subjects will be recruited from the ophthalmology clinic at GOSH, London. In addition, subjects will be recruited from the admissions ward prior to 48-hour ICP assessment and/or cranial vault expansion surgery, should this be their first stage of clinical care when referred to GOSH.

### Inclusion criteria

Patients aged 0–18.Clinical and/or genetic diagnosis of craniosynostosis, IIH, space occupying lesion or other conditions association with IH.

### Exclusion criteria

Patients older than 18 years of age.Patients not wishing to participate.Patients incapable of giving consent and without a legal guardian willing or able to do so.

### Information and consent process

Patients presenting to their pre-existing clinical appointments at GOSH, along with their family members/guardians, will be approached by the study investigator(s) and will be provided with the study information leaflet. Information leaflets suitable for children are also available. If children over 7 years old are able to understand the study, they will be given the option to provide their signature as a form of assent on the consent form along with their parent/guardian’s signature.

After the consent form is signed, patients will be taken to the investigator’s clinic room, or the handheld OCT scanner will be brought to them if appropriate, in order to acquire their OCT images. If it is not possible to take their scan on the same day, patients will be invited back to have their OCT scan at a suitable date in the near future. Where possible, subjects will have repeat OCT scans in future appointments to obtain longitudinal data. Consent will be taken in advance of ICP assessment or any surgical procedure requiring general anaesthesia.

### Outcome measures

Our primary outcome measures are OCT examinations and ICP assessments. Our primary OCT outcome measure is retinal nerve fibre layer (RNFL) thickness; other OCT parameters are listed below. OCT examination must be performed at the time of ICP assessment, or within 28 days prior to or 14 days following ICP assessment. Only one visit per child for OCT examination is required to fulfil the primary objective.

Our secondary outcome measures include the following, where possible:

Success rates of handheld OCT in children at risk of IH, particularly in craniosynostosis.Repeated OCT data between clinic visits±ICP assessments±cranial vault expansion surgery±follow up, with repeated ICP data if available.Fundoscopic examination within 3 months of OCT examination and/or at most recent follow-up visit.VA measured within 3 months of OCT examination and/or at most recent follow-up visit.Contrast sensitivity measured within 3 months of OCT examination and/or at most recent follow-up visit.Visual field testing within 3 months of OCT examination and/or at most recent follow-up visit.Visual evoked potentials (VEPs) within 3 months of OCT examination and/or at most recent follow-up visit.Comparison of the above measures with ICP and final VA, where available and appropriate.

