### Handheld OCT image acquisition and analysis

A non-contact, spectral domain handheld OCT scanner (Envisu C-2300, 3.3 µm axial resolution; Leica Microsystems, Wetzlar, Germany) will be used to scan the ONH and fovea. A 12×8 mm scanning window will be used in the acquisition protocol—this permits imaging of both the ONH and fovea in one scan. The three-dimensional raster scan for both scan sequences will consist of 100 B-scans and 500 A-scans per B-scan line resulting in a short acquisition time (1.9 s) enabling imaging of the ONH and fovea with minimal movement artefact. Handheld OCT will be performed at the time of 48-hour ICP monitoring to fulfil our primary objective; wherever possible, handheld OCT will also be performed during clinic visits to fulfil our secondary objectives. In awake children, visual devices including cartoons on smartphones and tablets will be used as appropriate. Where possible, an assistant can operate the controls to acquire images, otherwise the lead investigator ([name]) will acquire images alone using the foot pedal.

Our imaging protocol involves scanning the right eye followed by the left eye. Once the image is acquired, the en face view is used to identify the ONH, which is navigated frame by frame until the central slice featuring the deepest optic cup is identified for ONH analysis. For foveal segmentation, the fovea is navigated frame by frame until the central slice featuring the deepest foveal pit is identified. Scans are repeated twice per eye where possible, and any scans of non-analysable quality are discarded. Analysable quality is defined as an ONH tomogram wherein the edges of the disc margins and the cup profile, including its lowermost point, can be clearly visualised, or a foveal tomogram wherein it is possible to identify the foveal pit in full and all foveal layers from the external limiting membrane to Bruch’s membrane. In cases of papilloedema, the handheld OCT probe can be repositioned slightly forwards in the axial plane, or the reference arm can be lowered, until the entire swollen ONH is visualised without missing the disc margins. Using this technique, all cases with papilloedema were successfully imaged in our recent feasibility and repeatability study.^47^

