### Assessment of possible adverse effects

OCT is a safe and non-contact imaging technique that uses low-coherence light. It is extremely unlikely that any adverse events could arise during OCT imaging. Standard clinical care will continue during and beyond the completion of the RIO study.

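### The primary OCT may be taken up to 14 days after ICP assessment with no rule for scans that follow an intervention prompted by the result, which could lower measured sensitivity

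*Protocol article*

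**What the plan says.** All references are to the protocol article.

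- **Outcome measures** sets a binding window: "OCT examination must be performed at the time of ICP assessment, or within 28 days prior to or 14 days following ICP assessment". It adds: "Only one visit per child for OCT examination is required to fulfil the primary objective".
- **Handheld OCT image acquisition and analysis** gives a single time: "Handheld OCT will be performed at the time of 48-hour ICP monitoring to fulfil our primary objective". It assigns clinic-visit scans to the secondary objectives.
- **Recruitment** says that "subjects will be recruited from the admissions ward prior to 48-hour ICP assessment and/or cranial vault expansion surgery" where this is the child's first stage of care at the centre.
- **Information and consent process** has an ordering rule, but for consent: "Consent will be taken in advance of ICP assessment or any surgical procedure requiring general anaesthesia". Scanning follows consent, and a child who cannot be scanned that day is invited back later.
- **Assessment of possible adverse effects** says: "Standard clinical care will continue during and beyond the completion of the RIO study".
- **Secondary objectives** include: "To compare repeated OCT data between clinic visits±ICP assessments±cranial vault expansion surgery±follow up, with ICP assessments wherever possible".
- **Exclusion criteria** cover age, refusal and lack of valid consent. They do not mention treatment between the two tests.
- **Statistical analysis** does not separate scans by whether an intervention came first.

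**The concern.** A diagnostic accuracy estimate is meaningful when the index test and the reference standard describe the same state of the child. The window allows the scan to come after the ICP result is known, and no stated rule requires it to come before anything done in response. Since one OCT visit is enough, that late scan may be the child's only one.

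If a child with IH is treated after monitoring and the optic nerve appearance has regressed by the time of the scan, a child who would have been a true positive is counted as a false negative. This would fall mainly on IH-positive children, because they are the ones most likely to be treated on the strength of the result. Sensitivity is the quantity on which the sample size rests, so it is the one most exposed.

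The two timing statements also leave the primary set open. A clinic scan ten days after monitoring qualifies under Outcome measures, but reads as a secondary-objective scan under the acquisition section.

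**Working it through.** **1. The plan's own figure.** Sample size calculation gives fundoscopy sensitivity 22%, OCT sensitivity 62%, power 80%, α = 0.05 and n = 39. Entering 0.22 and 0.62 as the two discordant proportions of a two-sided McNemar test gives ψ = 0.84 and d = 0.40:

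n = [1.96·√0.84 + 0.8416·√(0.84 − 0.16)]² / 0.16 = 38.76, rounded up to 39; power at 39 is 80.3%.

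The figure reproduces, so nothing here rests on an arithmetic error.

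**2. What the text allows.** Three conditions must all hold for the bias to occur: an ICP-lowering intervention within 14 days after ICP assessment, a primary scan after that intervention, and loss of the OCT sign by the time of that scan. The article rules out none of them and gives a rate for none of them.

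**3. Size under stated assumptions.** Let f be the share of IH-positive children scanned after such an intervention, and suppose that half of those who would have shown the OCT sign have lost it. Then measured sensitivity = 0.62 × (1 − 0.5f).

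- f = 10%: 0.62 × 0.95 = 0.589, about 59%
- f = 25%: 0.62 × 0.875 = 0.5425, about 54%

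If all 39 children were IH-positive, that is 0.031 × 39 ≈ 1.2 and 0.0775 × 39 ≈ 3.0 true positives lost.

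**4. A wider range.** Let s be OCT sensitivity in the affected children. Measured sensitivity = (1 − f) × 0.62 + f × s. Power is Φ{[d√n − 1.96√ψ] / √(ψ − d²)}, with 0.22 and the measured sensitivity entered as in step 1. It takes all 39 children as IH-positive.

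| f | s | Measured sensitivity | Power at 39 | n for 80% power |
|---|---|---|---|---|
| any | 62% | 62% | 80.3% | 39 |
| 10% | 42% | 60% | 76.7% | 43 |
| 10% | 22% | 58% | 72.7% | 47 |
| 20% | 42% | 58% | 72.7% | 47 |
| 20% | 22% | 54% | 64.0% | 56 |
| 30% | 42% | 56% | 68.5% | 51 |
| 30% | 22% | 50% | 54.3% | 70 |

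Example: f = 20% and s = 22% give 0.8 × 0.62 + 0.2 × 0.22 = 0.54, so d = 0.32 and ψ = 0.76.

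If the two tests are instead taken as independent given IH, power at 39 over f = 10–30% and s = 22–42% is 71–92%. Neither f nor s is in the article. If the sign has not regressed, there is no loss.

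**5. Specificity.** At a fixed cut-off, late scans in IH-positive children leave specificity unchanged. Statistical analysis plans ROC curves, and the article fixes no cut-off. If the cut-off is taken from the curve, regressed IH-positive values can move it, and specificity with it.

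**The case against.** The strongest reply is that the two timing statements are compatible. The acquisition section gives the nominal time; Outcome measures repeats it and adds a tolerance. That is ordinary practice, and a reader who infers a flat contradiction goes further than the text. This stands: what is needed is alignment.

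The described workflow also points to early scans. Consent precedes ICP assessment or surgery, scanning follows consent, and ward recruitment takes place before monitoring or surgery. The post-ICP window looks like a fallback, so a large affected share seems unlikely. This also stands, but it describes expected practice and does not exclude the late scan.

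A reader might infer that the plan itself expects OCT to change with treatment, because a secondary objective compares scans around cranial vault surgery. That objective asks whether OCT changes; it does not say that it does, still less within 14 days. A reader might also infer that sensitivity is certainly biased downwards while specificity is safe. The article does not say that treatment follows only a positive result, and specificity is safe only at a fixed cut-off.

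Sampling error is large as well. With all 39 children IH-positive, the standard error of a 62% sensitivity is √(0.62 × 0.38 / 39) ≈ 7.8 points, against a shift of about 3 points at f = 10%.

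Finally, selection among several scans is often left to an analysis plan that is not shown. That would answer a complaint about missing detail. Here, however, the article fixes an eligibility window in binding terms, and that window, followed as written, admits the problem scans.

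**Conclusion.** The point holds in a limited form. The stated window can pair a reference result obtained before an intervention with an index test obtained after it, mainly in IH-positive children. This could lower measured sensitivity and, with a data-chosen cut-off, could also shift specificity.

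How much is unknown. The 59% and 54% figures rest on an assumed affected share of 10% or 25% and an assumed half of signs lost; with no regression the effect is zero. The documents do not support saying that the bias will occur or that it is large. The case for acting is that the route to bias is open in the text and cheap to close. More recruitment would narrow the confidence interval around such an estimate but would not correct it.

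**What to change.** 1. Align Outcome measures with the image acquisition section, for example by stating the time of 48-hour monitoring as the nominal time and the existing 28-day and 14-day limits as its tolerance.
2. State that the primary accuracy analysis uses, for each child, the OCT closest to ICP monitoring that lies within the window and was acquired before any ICP-lowering intervention following the ICP result.
3. Put scans taken after such an intervention in a sensitivity analysis, using the recorded OCT, ICP and intervention dates.

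The cost is a short addition to the text and an intervention date alongside the OCT and ICP dates. A few children whose only scan is late may leave the primary set, which matters somewhat in a cohort of 39, so their number should be reported. The change concerns only which scans count in the analysis; no change to treatment or its timing is proposed.
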